## Abstract

**Background:** Currently, an independent relationship between hearing loss and cognitive decline in older adults is suggested by large prospective studies. In general, cochlear implants improve hearing and the quality of life in severely to profoundly hearing impaired older persons. However, little is known about the effects of cochlear implantation on the cognitive evolution in this population.

**Aim of the study:** The primary goal of this prospective, longitudinal cohort study is to explore the cognitive profile of severely to profoundly postlingually hearing impaired subjects before and after cochlear implantation. In addition, the current study aims to investigate the relationship between the cognitive function, audiometric performances, quality of life, and self-reliance in these patients.

**Methods:** Twenty-five patients aged 55 or older, scheduled for cochlear implantation, will be enrolled in the study. They will be examined prior to implantation, at 6 and 12 months after implantation and annually thereafter. The test battery consists of (1) a cognitive examination, using the Repeatable Battery for the Assessment of Neuropsychological Status adapted for Hearing impaired persons (RBANS-H), (2) an audiological examination, including unaided and aided pure tone audiometry, speech audiometry in quiet and speech audiometry in noise, (3) the administration of four questionnaires evaluating quality of life and subjective hearing benefit and (4) a semi-structured interview about the self-reliance of the participant.

**Discussion:** Up until now only one study has been conducted on this topic, focusing on the short-term effects of cochlear implantation on cognition in older adults. The present study is the first study to apply a comprehensive neuropsychological assessment adapted for severely to profoundly hearing impaired subjects in order to investigate the cognitive capabilities before and after cochlear implantation.

**Trial registration:** The present protocol is retrospectively registered at Clinical Trials (ClinicalTrials.gov) on June 9th, 2016. The first participant was enrolled on June 22nd, 2015. The protocol identifier is NCT02794350.

## Background

Over the past decade the relationship between hearing loss and cognitive decline in the older population has gained more research interest. Large prospective studies have found an independent relationship between hearing loss on the one hand and age-related cognitive decline and incident dementia on the other hand (Lin et al., 2011, 2013; Gallacher et al., 2012; Gurgel et al., 2014). The basis of this association remains unclear. For instance, hearing loss may accelerate cognitive decline in older adults and therefore may be a risk factor of this pathology. Alternatively, hearing loss could be an early symptom of cognitive decline and could be an effect rather than a cause of the cognitive impairment. A common cause that influences both pathologies may be a third underlying mechanism of the association between hearing loss and cognitive decline (Martini et al., 2014; Peracino, 2014). As hearing aids can improve the hearing and contribute to reestablishing the individual's participation in society, they could have a positive effect on the expected trajectory of cognition. However, the results of studies investigating the effect of hearing aids on cognitive function in older adults are variable (Allen et al., 2003; van Hooren et al., 2009; Acar et al., 2011; Magalhaes and Iorio, 2011; Kalluri and Humes, 2012; Amieva et al., 2015; Dawes et al., 2015; Meister et al., 2015). Moreover, in case of a positive relationship between hearing aid use and cognition, the direction of causality is not clear. Rather than hearing aid use improving cognitive abilities, individuals who are cognitively well-functioning, may tend to seek and obtain hearing aids more often (Dawes et al., 2015). Very limited research has been conducted concerning the impact of cochlear implantation on the cognitive capabilities of older adults. Miller et al. (2015) provided an overview of existing literature on the question as to whether cochlear implantation in older adults with a severe to profound hearing loss modifies the expected evolution of cognitive decline. Based on the reviewed articles, the authors concluded that there is a lack of well-designed prospective studies evaluating changes in cognition after cochlear implantation. Recently, Mosnier et al. (2015) published a multi-center, prospective, longitudinal study concerning the impact of cochlear implantation on the cognitive capabilities in 94 adults aged 65–85 years. The investigators established improvements in preoperatively impaired cognitive capabilities at 6 months and 1 year after implantation.

The first goal of this longitudinal cohort study is to explore prospectively the cognitive profile of severely to profoundly hearing-impaired patients aged 55 or more, before and after cochlear implantation, both in the short term and the long term. Secondly, the aim is to investigate the relationship between the cognitive function, audiometric performances, quality of life and self-reliance in these patients.

## Methods

### Study protocol

This is a single-center, currently ongoing study, conducted at the Rehabilitation Center for Communication Disorders of the Department of Otorhinolaryngology of the Antwerp University Hospital, Belgium. Subjects are invited to participate in the study if they meet the following inclusion criteria: (1) The subject meets the Belgian national criteria for reimbursement of a cochlear implant, (2) the subject suffers from a postlingual hearing impairment, (3) the subject is scheduled for a first cochlear implantation and (4) the subject is aged 55 or older. The national criteria for reimbursement of a cochlear implant are (A) bilateral severe to profound hearing loss (pure tone average at 500, 1000, and 2000 Hz equal to or exceeding 85 dB HL), (B) brainstem evoked response audiometry results in a threshold of peak V at 90 dB nHL or more and (C) speech recognition scores of 30% or less for Dutch open-set monosyllabic words presented at 70 dB SPL in quiet in the best aided condition. Subjects who do not meet the national criteria for reimbursement and pay the implantation themselves are not included in the study. The case is multidisciplinary evaluated, all contra-indications for cochlear implantation are to be taken into account and the expectations of the person toward the rehabilitation process and the outcomes are thoroughly discussed by the clinician to remain realistic.

The participants are evaluated by an experienced, Good Clinical Practice (GCP) certificated audiologist (Master of Science) prior to implantation and subsequently 6 months and 12 months after activation of the speech processor and annually from then on (Table 1). The test battery consists of a cognitive assessment to evaluate five different cognitive domains, an audiological examination, four questionnaires to assess the impact of the hearing disability and the quality of life (QoL), and a semi-structured interview in which the self-reliance of the patient is discussed.

**Table 1 T1:** **Time schedule of assessments and intervention**.

	**Preoperatively**	**Cochlear implantation**	**6 months** after first fitting	**12 months** after first fitting	**yearly**
					
Cognition	RBANS-H		RBANS-H	RBANS-H	RBANS-H
MOM	Tone audiometry		Tone audiometry	Tone audiometry	Tone audiometry
	- unaided (inserts)		- unaided (inserts)	- unaided (inserts)	- unaided (inserts)
	- aided (free field)		- aided (free field)	- aided (free field)	- aided (free field)
	Speech audiometry in quiet (NVA)		Speech audiometry in quiet (NVA)	Speech audiometry in quiet (NVA)	Speech audiometry in quiet (NVA)
	- unaided (headphones)		- aided (free field)	- aided (free field)	- aided (free field)
	- aided (free field)				
	Speech audiometry in noise (LIST)		Speech audiometry in noise (LIST)	Speech audiometry in noise (LIST)	Speech audiometry in noise (LIST)
	- unaided (headphones)		- aided (free field)	- aided (free field)	- aided (free field)
	- aided (free field)				
	HISQUI_19_		HISQUI_19_	HISQUI_19_	HISQUI_19_
Subjective benefit, Self-reliance, CI usage	Questionnaires		Questionnaires	Questionnaires	Questionnaires
	- NCIQ		- NCIQ	- NCIQ	- NCIQ
	- SSQ12		- SSQ12	- SSQ12	- SSQ12
	- HADS		- HADS	- HADS	- HADS
	Interview		Interview	Interview	Interview

### Primary outcome measurement: RBANS-H

The primary outcome measurement is the change in cognitive capabilities following implantation, as measured by means of the Repeatable Battery for the Assessment of Neuropsychological Status (RBANS, Randolph et al., 1998), adjusted to test Hearing impaired subjects (RBANS-H). The RBANS assesses five cognitive domains, i.e., *Immediate Memory, Visuospatial/constructional, Language, Attention*, and *Delayed Memory* (Table 2). The test consists of 12 subtests and the score on each subtest contributes to one of the five domains. The Dutch version of the original English RBANS is obtained by the process of forward-backward translation. In order to test subjects with a severe hearing impairment a number of adjustments to the standard RBANS had to be made (Phillips, 2016). The administration of the test is accompanied by the use of a PowerPoint presentation shown on an external computer screen connected to a laptop. By means of this presentation all the oral instructions are supported by written explanations to ascertain that the subject understands the instruction even though he or she does not hear what is being said. In addition, the stimuli in the subtests *List Learning, Story Memory, Digit Span*, and *List Recognition* are not only presented auditorily but also visually, making it possible to test the subject in the same reliable way before and after implantation. All the adjustments were made in accordance to the guidelines of the RBANS, as discussed in the manual on page 15 “Testing Examinees With Physical or Language Impairments” (Randolph, 2012). The RBANS was ordered on the website of Pearson Clinical (http://www.pearsonclinical.com).

**Table 2 T2:** **The five cognitive domains and twelve subtests of the RBANS**.

**Immediate memory**	**Visuospatial/ constructional**	**Language**	**Attention**	**Delayed memory**
(1) List Learning	(3) Figure Copy	(5) Picture Naming	(7) Digit Span	(9) List Recall
(2) Story Memory	(4) Line Orientation	(6) Semantic Fluency	(8) Coding	(10) List Recognition
				(11) Story Recall
				(12) Figure Recall

The domain *Immediate Memory* consists of two subtests: *List Learning* and *Story Memory*. In the first subtest, 10 semantically unrelated words are orally and visually presented to the subject. The words are presented on an external screen in lowercase e letters at a 2-s rate. Within the 2-s period the item is visible to the subject for 1.25 s, followed by a 0.75-s interval between the items. The examiner reads the words aloud when they appear on the screen so the subject receives audio-visual information. The subject is asked to repeat as many words as possible after each of four learning trials. In the second subtest, *Story Memory*, a twelve-item short story is presented over two trials. The story is presented visually in three separate parts and read aloud simultaneously at a slow reading speed. After each presentation the subject is asked to recall as much of the story as he or she can remember. A verbatim criterion is used.

The next two subtests, *Figure Copy* and *Line Orientation*, contribute to the second cognitive domain *Visuospatial/constructional*. The first subtest involves copying a geometric figure comprising ten parts, each evaluated for correctness and completeness on the one hand and proper location in relation to the rest of the figure on the other hand. The figure remains visually available while copying. In the second subtest of the *Visuospatial/Constructional* domain, a series of 13 identical lines, radiating out from a single point and spanning 180 degrees, are shown. Below this semi-circular, fan-shaped pattern of numbered lines (1–13), two lines of equal length that match two of the lines from the array are displayed. The subject is asked to give the numbers or point to the two lines that are identical in orientation to the two target lines.

The cognitive domain *Language* includes the subtests *Picture Naming* and *Semantic Fluency*. In the first subtest, 10 line drawings are to be named by the subject. In case of an obvious misperception, a semantic cue is given. The second subtest involves the generation of as many examples as possible from a given semantic category such as fruits and vegetables within 1 min.

The subtest *Digit Span* and the subtest *Coding* contribute to the domain *Attention*. The first of these two subtests is comparable to the subtest *Digits Forward* on the WAIS (Wechsler, 1955). In this test, a string of digits is read aloud and simultaneously shown on the computer screen. Each digit is visible for 1 s with a 0.75-s interval between the digits. The subject is asked to repeat the string in the same order. The length of the string increases by one, from two to nine digits. Two strings are provided for each length, but the second string of the same length is only read if the first one failed. In the subtest *Coding*, a page filled with symbols is presented to the subject and the subject is asked to fill in the number corresponding to each symbol using the key on top of the page. In this key the nine simple symbols are represented horizontally with the corresponding number (1–9) underneath it. The score is calculated as the total number of items correctly completed within 90 s.

The domain *Delayed Memory* comprises four subtests: *List Recall, List Recognition, Story Recall*, and *Figure Recall*. In the *List Recall* subtest, the subject is asked to recall as many words as he or she can remember from the list of 10 words learned previously in the *List Learning* subtest. In the subtest *List Recognition*, 20 words are audio-visually presented to the subject of which 10 words were on the original list (targets) and 10 were not (distractors). The 20 words in this test are transcribed on the screen. The examiner shows the next word at a variable speed depending on the reaction speed of the subject and reads the word aloud when it is shown on the screen. The subject is asked to declare whether each word was on the original list or not. In the *Story Recall* subtest, the subject is asked to recall as many details as he or she can from the story learned in the *Story Memory* subtest. In the last subtest, *Figure Recall*, the subject is asked to draw all the elements of the figure from the *Figure Copy* subtest that he or she can recall without visual display of the figure.

### Secondary outcome measurements

#### Audiological examination

In all subjects an audiological follow-up test is performed which is called the Minimal Outcome Measurements (MOM) (Kleine Punte and Van de Heyning, 2013) (Table 1). This examination includes pure tone audiometry, speech audiometry in quiet, speech audiometry in noise performed in a sound booth and the Hearing Implant Sound Quality Index (HISQUI_19_) (Amann and Anderson, 2014).

##### Unaided and aided hearing thresholds

According to current clinical standards (ISO 8253-1, 2010), unaided pure tone audiometry for air conduction is performed at 125, 250, 500, 1000, 2000, 3000, 4000, 6000, and 8000 Hz using a 2-channel Interacoustics AC-40 audiometer and insert earphones in a sound treated booth. Bone conduction thresholds are tested at 250, 500, 1000, 2000, 3000, and 4000 Hz. The best-aided thresholds with hearing aid(s) and/or cochlear implant (CI) are measured through free field audiometry with warble tones. The loudspeaker is placed at a distance of one meter in front of the subject at ear level. The thresholds are tested at 125, 250, 500, 1000, 2000, 3000, 4000, 6000, and 8000 Hz. If the subject wears two hearing systems, either two hearing aids (preoperatively) or a hearing aid and a CI (postoperatively), the benefit with each hearing system separately is measured as well.

##### Speech audiometry in quiet

Speech reception in quiet is measured using the Dutch open-set NVA lists developed by the Nederlandse Vereniging voor Audiologie (NVA) or Dutch Society for Audiology (Wouters et al., 1994; Bosman et al., 1995). Each list consists of 12 monosyllabic words (consonant-vowel-consonant) of which one is a training item. One list is presented at 65 dB SPL, by means of headphones (unaided, preoperatively) or in free field (aided, pre- and postoperatively) with a loudspeaker at 0° azimuth. The speech recognition score is the percentage of correctly identified phonemes.

##### Speech audiometry in noise

The speech reception in noise is assessed by means of the Leuven Intelligibility Sentences Test (LIST) using an adaptive procedure (van Wieringen and Wouters, 2008). This speech material is developed to quantify the speech understanding in subjects with severely impaired hearing. The frequency spectrum of the noise signal is equal to the long-term average speech spectrum of the sentences. The level of the noise is fixed at 65 dB SPL, while the level of the speech signal is altered depending on the response of the patient. If the subject repeats the keywords of the sentence correctly, the level of the next sentence is decreased by 2 dB SPL. If the subject fails to repeat the keywords, the level is increased by 2 dB SPL. Each list consists of 10 sentences and the speech reception threshold (SRT) is calculated as the mean level of the last five sentences together with the level of the imaginary 11th sentence of the list. This speech in noise test is performed preoperatively in an unaided situation using headphones and both pre- and postoperatively in an aided, free field situation with the loudspeaker in front of the subject at a distance of one meter.

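### The printed LIST scoring rule records a list with no correct sentence as a threshold of start level + 15 dB; such lists should be coded as not measurable and analysed as censored or worst rank

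*Protocol article*

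**What the plan says.** The protocol article, under Speech audiometry in noise, sets out the whole scoring procedure for the LIST:

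- Noise: "The level of the noise is fixed at 65 dB SPL".
- Step down: "If the subject repeats the keywords of the sentence correctly, the level of the next sentence is decreased by 2 dB SPL".
- Step up: "If the subject fails to repeat the keywords, the level is increased by 2 dB SPL".
- Length: "Each list consists of 10 sentences".
- Score: "the speech reception threshold (SRT) is calculated as the mean level of the last five sentences together with the level of the imaginary 11th sentence".

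The starting speech level is not given. No outcome other than a number is described. Before implantation the test is done unaided by headphones and aided in free field; after implantation it is done aided only (same section and Table 1).

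Under Study protocol, entry requires a bilateral "pure tone average at 500, 1000, and 2000 Hz equal to or exceeding 85 dB HL" and "speech recognition scores of 30% or less for Dutch open-set monosyllabic words presented at 70 dB SPL in quiet in the best aided condition".

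Under Statistics and anticipated results, floor and ceiling effects are to be summarised descriptively. No consequence for coding or analysis is attached to them.

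**The concern.** An up-down procedure estimates a threshold only if the level comes to hover around the point where the patient sometimes succeeds. Over ten sentences in 2 dB steps the level can rise by only 18 dB before the list ends. A patient whose threshold lies well above that range fails every sentence, and the rule still averages six levels and reports the result as an SRT. The value then depends on where the test began and not on the patient.

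The study admits people with very poor hearing and tests them in noise before implantation, so this can happen at baseline.

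The LIST is a secondary outcome. It is also one of the audiometric measures behind the second aim, which relates hearing performance to cognition, quality of life and self-reliance. A capped aided baseline shrinks the apparent change after implantation, and it merges patients with different hearing into one value fixed by the start level. With a target of 25 patients, a few such values can carry weight.

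**Working it through.** **Inputs.** From Speech audiometry in noise: noise N = 65 dB SPL, steps of +2 and -2 dB, 10 sentences, and a score that is the mean of levels 6 to 10 and the implied 11th. The start level S is not stated, so it is varied from 45 to 85 dB SPL as an assumption. The article gives no SRT figure to reproduce.

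**1. A list with ten failures.** Sentence k is presented at S + 2(k - 1). Sentences 6 to 10 are at S+10, S+12, S+14, S+16 and S+18, and the implied 11th is at S+20.

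SRT = S + (10 + 12 + 14 + 16 + 18 + 20)/6 = S + 90/6 = S + 15.

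| Start S (dB SPL) | Recorded SRT (dB SPL) | SRT minus noise (dB SNR) |
|---|---|---|
| 45 | 60 | -5 |
| 50 | 65 | 0 |
| 55 | 70 | +5 |
| 60 | 75 | +10 |
| 65 | 80 | +15 |
| 70 | 85 | +20 |
| 75 | 90 | +25 |
| 80 | 95 | +30 |
| 85 | 100 | +35 |

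The recorded threshold lies below two levels, S+16 and S+18, at which the patient failed.

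**2. The number does not give itself away.** If only the tenth sentence is correct, the implied 11th falls to S+16 and the SRT is S + 86/6 = S + 14.3. A list with one success and a list with none differ by 0.7 dB.

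**3. How far the score follows the start level.** Simulation of the printed rule with an assumed logistic curve, p = 1/(1 + exp(-4 × slope × (level - true SRT))), and an assumed slope of 10% per dB. Mean recorded SRT, in dB SNR:

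| True SRT | Start 55 dB SPL | Start 65 dB SPL | Start 75 dB SPL |
|---|---|---|---|
| 0 | -1.0 | 0.0 | +1.0 |
| +5 | +2.4 | +4.7 | +5.3 |
| +10 | +4.3 | +8.9 | +10.0 |
| +20 | +5.0 | +14.3 | +18.9 |
| +30 | +5.0 | +15.0 | +24.3 |
| +40 | +5.0 | +15.0 | +25.0 |

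At slopes of 5% and 17% per dB, a true SRT of +30 or +40 gives +5.0, then +14.5 to +15.0, then +22.5 to +25.0 for the three starts. The pattern is the same. For a threshold near the start level the rule works: at a true SRT of 0 the three starts agree within about 1 dB of the truth at 10% and 17% per dB, and within about 2.7 dB at 5% per dB.

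**4. Effect on change, as an illustration.** Take an aided true SRT of +30 dB SNR before and +5 after implantation, with start 65 dB SPL both times. The true change is 30 - 5 = 25 dB. The recorded change is 15.0 - 4.7 = 10.3 dB.

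**5. How often.** The documents hold no speech-in-noise data. Under start 65 dB SPL and 10% per dB, the chance of ten failures is 49% for a patient with a true SRT of 85 dB SPL and 90% at 90 dB SPL. These figures are conditional on those thresholds. They say nothing about how many patients have them.

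**The case against.** The best defence is that a journal article condenses a cited test procedure. The start level and the coding of a failed list may stand in the full protocol or the test instructions, and their absence is no error. The entry criteria concern isolated monosyllables in quiet, with up to 30% correct allowed, so they do not select people who can repeat no sentence. The material is described as developed for severely impaired hearing. Floor and ceiling effects are foreseen in the statistics section. Aided thresholds and NVA phoneme scores are collected as well, and no particular LIST correlation is specified. With a common start level, failed lists tie at one value, as they also would under worst-rank coding.

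Much of this stands. The missing start level is not held against the article, and the frequency of failed lists is unknown. What remains is that the article prints a full scoring rule, and that rule assigns a number to a list with no correct answer. For HISQUI19 the same article does say how unanswered items are scored. A descriptive note on floor effects does not change the values analysed. A worst-rank tie also differs from the printed score: it does not depend on the start level and claims no measured distance.

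Three stronger readings are tempting and are not supported:

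- *That the failed list looks normal.* From a 65 dB SPL start it is +15 dB SNR, a poor score. It reaches 0 dB SNR or better only if the start is 50 dB SPL or lower, and the article gives no normal range.
- *That many baseline values will be of this kind.* Nothing in the article allows a count.
- *That the unaided run biases the change after implantation, or that its noise is certainly inaudible.* The unaided test has no postoperative counterpart. Pure-tone dB HL and speech-noise dB SPL are different scales, so setting 85 against 65 is only indicative.

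**Conclusion.** The point holds in a limited form. That ten failures score exactly start + 15 dB is arithmetic from the printed rule and rests on no assumption; only the figure of 80 dB SPL depends on an assumed 65 dB SPL start. That such lists occur before implantation is plausible from the entry criteria, more so unaided than aided, but cannot be quantified. Where they occur in the aided baseline, they would understate the change after implantation and tie the relationship analyses to the start level. The loss can be large for the patient concerned (10.3 dB recorded against 25 dB true in the illustration, under an assumed slope and assumed thresholds).

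The primary RBANS-H analysis and the sample size are untouched, and the study calls itself exploratory. This is a minor to moderate improvement to one secondary outcome.

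**What to change.** Under Speech audiometry in noise, add that a list with no correctly repeated sentence is recorded as 'SRT not measurable' and not as the computed mean. In pre/post comparisons and correlations, analyse it as right-censored above the highest level actually presented (S + 18, since the 11th sentence is only implied) or as the worst rank. Report the number of such lists by visit and condition. Treat the unaided preoperative LIST as descriptive only.

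Two variants should be avoided. A rule based on the absence of reversals would also catch a list with all ten sentences correct and could code the best performer as worst. Replacing the SRT by the NVA score only at visits where the SRT fails would mix two scales, with the outcome itself deciding which is used. If the NVA score serves the relationship analyses, it should do so for all patients and visits.

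The cost is one sentence of scoring and a censored or rank-based analysis of one secondary outcome. No testing is added. Some baseline SRTs lose a numeric value. The rule removes only the clear case: lists with one or two late successes remain compressed towards the same limit.
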